#### 2.3.2. Exclusion criteria.

Patients with genital tract malformation or other reproductive system diseases (adenomyosis, endometrial tuberculosis, etc);Suffering from sexually transmitted diseases or acute inflammation of urogenital system;Patients with serious primary diseases such as cardiovascular, cerebrovascular, kidney, liver and hematopoietic system;Patients with serious cognitive impairment and mental illness;Long term exposure to toxic and harmful substances such as radiation or chemicals;Incomplete data or unauthorized use of other treatments;Patients who are allergic to the drugs used in this study.

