## 2. Methods

### 2.1. Trial design

This study is a protocol for a randomized, non-blinded, controlled clinical trial. A total of 180 infertile patients with the type of Deficiency of both spleen and kidney will be conducted according to the flow diagram and will last for near 2 years, scheduled to start from January 2023 (Fig. 1).

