### 2.3. Participants

#### 2.3.1. Inclusion criteria.

Patients who meet the diagnostic criteria for infertility and spleen kidney deficiency syndrome;Patients who plan to perform ART in the Reproductive Department of Run Run Shaw Hospital affiliated to Zhejiang University and plan to perform frozen embryo transfer; the transferred embryos are 2 superior embryos;25 to 40 years old;Patients who have been insured in Hangzhou TCM Hospital Affiliated to Zhejiang Chinese Medical University after embryo transfer;Signed informed consent.

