### 2.4. Randomization and blinding

The randomization succession will be created with the PROC PLAN strategy explanations of SAS programming 9.3 bundle by the analyst specialists of Zhejiang Chinese Clinical College, and will be hidden and scattered utilizing obscure envelopes. During the time spent treating and analyzing the data, these specialists will not be involved. By phone, the clinical investigators will apply for a new included patient’s randomization number. The doctors and patients engaged in this RCT won’t likely be rendered blind because there is no usage of herbal medicine in the control group.

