### 2.5. Interventions

The randomization strategy will be used to divide the participants into one of the 2 groups.

The treatment group: conventional western medicine after embryo transplantation combined with Jian-Pi-An-Tai formula. Jian-Pi-An-Tai formula is composed of codonopsis pilosula, astragalus membranaceus, fried atractylodes macrocephala, donkey hide gelatin, mulberry parasitic, dodder seed, raw rehmannia root, cooked rehmannia root, ramie root, scutellaria baicalensis, paeony root, wolfberry fruit, eclipta alba, perilla frutescens stem, licorice root, and dipsacus, which provided by Preparation Center of the Hangzhou TCM Hospital Affiliated to Zhejiang Chinese Medical University. The patients are planned to take Jian-Pi-An-Tai formula for 5 weeks.

The control group: conventional western medicine after embryo transplantation.

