### 2.6. Outcome measures

#### 2.6.1. Primary outcome measures

Embryo implantation rate: number of embryos implanted/total number of embryos transferred * 100%. Blood sampling test of β-HCG will be taken on the 8th and 10th days after embryo transfer. Positive results can be determined as successful embryo implantation.Clinical pregnancy rate: number of clinical pregnancies/number of implanted embryos * 100%. Doppler ultrasound will be taken on the 5th week after embryo transfer. Gestational sac and fetal heart beat can be determined as successful clinical pregnancy.Persistent pregnancy rate: number of cycles of continuous pregnancy/number of embryos implanted * 100%. Doppler ultrasound will be taken on the 12th week after embryo transfer. Existence of fetal heart beat can be determined as successful persistent pregnancy.

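### An exclusion criterion for incomplete data and unauthorised other treatment has no time limit, so in an open trial it can remove women after randomisation

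*Protocol article*

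**What the plan says.** Section 2.3.2 places "Incomplete data or unauthorized use of other treatments" in the same list as baseline conditions such as genital tract malformation and drug allergy. It does not say when the item applies.

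Section 2.1 describes a "randomized, non-blinded, controlled clinical trial". Section 2.4 explains the lack of blinding: "The doctors and patients engaged in this RCT won’t likely be rendered blind", "because there is no usage of herbal medicine in the control group".

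Treatment and follow-up extend well beyond entry. Section 2.5 states: "The patients are planned to take Jian-Pi-An-Tai formula for 5 weeks". Section 2.6.1 sets β-HCG tests on days 8 and 10 and a scan at week 5, and then: "Doppler ultrasound will be taken on the 12th week after embryo transfer". The symptom form is repeated after 5 weeks (section 2.6.2.1).

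The inclusion list in section 2.3.1 refers to two different times. One item requires that women "plan to perform frozen embryo transfer"; another asks for "Patients who have been insured in Hangzhou TCM Hospital Affiliated to Zhejiang Chinese Medical University after embryo transfer".

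**The concern.** An exclusion criterion should rest on facts known before allocation. Whether follow-up data are complete, and whether a woman departs from the trial regimen, is mostly learned afterwards. If either leads to exclusion, women who were randomised leave the comparison.

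Such removal need not be neutral. Doctor and patient know the arm throughout and know the β-HCG result weeks before the later scans. A woman with a negative test may have less reason to return. A control who wanted herbal treatment may be more likely to seek it elsewhere. Both are plausible inferences, not statements in the protocol. Staff who judge whether data are incomplete or a treatment unauthorised can know both arm and early outcome. What is at stake is the protection that randomisation gives to the primary comparisons.

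**Working it through.** **Inputs.** Total of 180 women, 10% drop-out, response rates 86.2% and 54.2%, alpha 0.05 and beta 0.2 (section 2.8); two-sided tests (section 2.9); two embryos per transfer (section 2.3.1). Assumptions not in the document: 1:1 allocation (90 per arm), randomisation before the day-8 test, and a common true success rate per woman of 50% (range 40% to 54.2%).

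**The plan's own figure.** The plan gives no number for removals under this criterion. The nearest are the 10% drop-out and the total of 180. The stated rates with two-sided 0.05 and 80% power give 31 per arm; 31/0.9 = 34.4, so 35 per arm and 70 in total. With continuity correction: 37 per arm; 37/0.9 = 41.1, so 42 per arm and 84 in total. The 180 is not reproduced, but that is a separate matter and this point does not depend on it. At the plan's rates, power is 99.8% with 90 per arm and 99.6% with 81, so the criterion has almost no bearing on power; its cost is bias.

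**Step 1: what can be known, and when.**

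| Reason for exclusion | Knowable before randomisation? |
|---|---|
| Missing screening data | Yes |
| Other treatment in use at entry | Yes |
| Unauthorised treatment during the 5-week course | No |
| Missed week-5 symptom form or scan | No |
| Missed week-12 scan | No |

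The wording covers all five rows. Only the first two belong in an eligibility list.

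**Step 2: illustration per woman, no true effect.** With S successes among n women and r failures removed, the observed rate is S/(n − r). Here S = 0.50 × 90 = 45, and r = 10% of 90 = 9.

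- Failures removed from one arm only: 45/(90 − 9) = 45/81 = 55.6% against 45/90 = 50.0%, a false difference of 5.6 points.
- Failures removed equally from both arms: 45/81 = 55.6% in each, difference 0, both rates inflated by 5.6 points.

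**Step 3: effect on the test.** The 9 women are 20% of the 45 failures. If 20% of failures are removed from one arm only, the false difference is about 5.5 points across true rates of 40% to 54.2%, and the two-sided type I error rises from 5% to about 11% (normal approximation to the chi-square test). With 10% removed from one arm, the figures are about 2.6 points and 6.4%. With 20% removed from one arm and 10% from the other, they are about 2.9 points and 6.6%.

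**Step 4: the denominators in section 2.6.1.** Step 2 counts women. The protocol divides implantation by embryos transferred, and the other two primary rates by embryos implanted. Taken literally:

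- Removing a β-HCG-negative woman takes 2 embryos from the implantation denominator and none from its numerator. For 9 such women in one arm, the denominator falls from 90 × 2 = 180 embryos to 81 × 2 = 162, so that arm's implantation rate is multiplied by 180/162 = 1.11.
- The same woman contributes nothing to the numerator or denominator of the clinical or persistent pregnancy rate, so her removal changes neither.
- Removing a β-HCG-positive woman, for a missed scan or for other treatment, can change all three rates.

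**The case against.** **A baseline reading is possible.** Missing screening data and other treatment at entry can both be known before randomisation, and section 2.4 issues a number to a newly included patient, which suggests that eligibility comes first. The article nowhere says outright that randomised women will be deleted. This stands as a limit on certainty. It does not remove the point, because the item carries no such restriction, and unauthorised use reads most naturally as conduct under the trial regimen.

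**Analysis sets belong in the analysis plan.** That is true, and a missing definition of the analysis set is not the complaint. Eligibility criteria are protocol content, and an analysis plan that kept all randomised women would have to contradict this one.

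**The loss described comes after implantation is measured.** The days 8 and 10 result is in hand before later visits are missed, so the implantation rate suffers only if exclusion drops the woman from every analysis. The text does not say so explicitly, but an exclusion criterion ordinarily applies to the patient and not to one outcome.

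**Stronger readings a reader might infer.** One is that incomplete data simply stands for failure and so inflates all the pregnancy rates. The literal denominators do not support this for β-HCG-negative women (step 4). Another is a false difference of 11 points: 36/81 = 44.4% against 45/81 = 55.6%. That needs 9 pregnant controls and 9 non-pregnant treated women to be removed. It is an extreme bound, and nothing in the documents makes it likely. A third is that the inclusion list has the same fault. It does not: the conflict there concerns the time of enrolment, and the word insured is not shown to mean that care has already been received.

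**Conclusion.** The point holds as a fault in a stated rule. The criterion has no time limit and, in an open trial with 5 weeks of treatment and outcomes to week 12, allows randomised women to be removed for post-allocation events. The direction and size of any bias cannot be derived from the documents.

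The 5.6-point figure is an illustration. It rests on 90 women per arm, a 50% success rate per woman in both arms, and removal of 9 failures from one arm only. Smaller or more balanced removal gives less, down to no false difference when failures are removed equally. The inclusion timing is a separate and weaker wording conflict.

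**What to change.** 1. Delete the item from section 2.3.2, or restrict it to facts known before randomisation: missing screening data and other treatment at entry.
2. State that the primary comparison keeps all randomised women in their assigned arm, including those who use other treatments or miss visits.
3. Seek pregnancy status by phone for women who stop attending. Count those with no documented pregnancy as not pregnant, and add a sensitivity analysis for unknown outcomes. This requires rates per randomised woman.
4. Separately, reconcile the two inclusion items in section 2.3.1 so that eligibility is complete and the randomisation number released at one fixed point before the day-8 β-HCG test.

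The cost is protocol wording, some phone follow-up, and slight dilution of the estimated effect by non-adherence.

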### 2.4. Randomization and blinding

The randomization succession will be created with the PROC PLAN strategy explanations of SAS programming 9.3 bundle by the analyst specialists of Zhejiang Chinese Clinical College, and will be hidden and scattered utilizing obscure envelopes. During the time spent treating and analyzing the data, these specialists will not be involved. By phone, the clinical investigators will apply for a new included patient’s randomization number. The doctors and patients engaged in this RCT won’t likely be rendered blind because there is no usage of herbal medicine in the control group.

### 2.5. Interventions

The randomization strategy will be used to divide the participants into one of the 2 groups.

The treatment group: conventional western medicine after embryo transplantation combined with Jian-Pi-An-Tai formula. Jian-Pi-An-Tai formula is composed of codonopsis pilosula, astragalus membranaceus, fried atractylodes macrocephala, donkey hide gelatin, mulberry parasitic, dodder seed, raw rehmannia root, cooked rehmannia root, ramie root, scutellaria baicalensis, paeony root, wolfberry fruit, eclipta alba, perilla frutescens stem, licorice root, and dipsacus, which provided by Preparation Center of the Hangzhou TCM Hospital Affiliated to Zhejiang Chinese Medical University. The patients are planned to take Jian-Pi-An-Tai formula for 5 weeks.

The control group: conventional western medicine after embryo transplantation.

### 2.6. Outcome measures

#### 2.6.1. Primary outcome measures

Embryo implantation rate: number of embryos implanted/total number of embryos transferred * 100%. Blood sampling test of β-HCG will be taken on the 8th and 10th days after embryo transfer. Positive results can be determined as successful embryo implantation.Clinical pregnancy rate: number of clinical pregnancies/number of implanted embryos * 100%. Doppler ultrasound will be taken on the 5th week after embryo transfer. Gestational sac and fetal heart beat can be determined as successful clinical pregnancy.Persistent pregnancy rate: number of cycles of continuous pregnancy/number of embryos implanted * 100%. Doppler ultrasound will be taken on the 12th week after embryo transfer. Existence of fetal heart beat can be determined as successful persistent pregnancy.

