### 2.9. Statistical analysis

The statistical analysis of this study will be conducted by statisticians of the Zhejiang Chinese Medical University. Software packages SPSS 23.0 and SAS 9.3 will be used for statistical analysis. All statistical tests will be conducted by 2-sided tests and *P* values less than .05 are considered statistically significant. The description of quantitative indicators will calculate the number of cases, mean, standard deviation, median, minimum and maximum. Classification indicators are described by the number of cases and percentages of each category. Normally distributed data is represented by mean ± standard deviation, and non-normally distributed data is represented by median and interquartile range. Comparisons between groups of measurement data will be conducted by using independent sample *t* test, and within group differences will be tested with paired *t* test. Differences between groups of numeration data will be assessed with chi-square test.

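### The first primary outcome counts embryos but is decided by a β-HCG result per woman, so its numerator cannot be obtained; if embryos stay the denominator, a plain chi-square test does not hold 5%

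*Protocol article*

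**What the plan says.** Section 2.6.1 gives the first primary outcome as a ratio of embryos: "number of embryos implanted/total number of embryos transferred". The measurement follows directly: "Blood sampling test of β-HCG will be taken on the 8th and 10th days after embryo transfer", and then "Positive results can be determined as successful embryo implantation". No other criterion for implantation is given.

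Section 2.3.1 fixes the number of embryos per woman: "the transferred embryos are 2 superior embryos". Section 2.5 makes the woman the unit of randomisation: "The randomization strategy will be used to divide the participants into one of the 2 groups".

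Section 2.9 states one between-group test for counts: "Differences between groups of numeration data will be assessed with chi-square test". It names no outcome and does not mention dependence between embryos of the same woman.

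The other two primary outcomes in 2.6.1, the clinical and the persistent pregnancy rate, both take the number of implanted embryos as their denominator.

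**The concern.** The definition and the measurement work on different units. A positive or negative blood test classifies the woman. Repeating it on days 8 and 10 gives two readings of the same woman, not one reading per embryo. The rule uses positivity alone, so nothing in it separates one implanted embryo from two.

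Two consequences follow.

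- **The outcome is undetermined.** Two analysts with the same data could report rates that differ by a factor of two. All three primary outcomes are affected, because the other two divide by the same unmeasured count.
- **The test may not hold its level.** If the ratio is analysed as written, up to 180 × 2 = 360 embryos enter a test that assumes independent units, while only 180 women are randomised. The p-value then has the wrong reference distribution. The direction of the error depends on the missing conversion rule.

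**Working it through.** **Inputs from the article.** Two embryos per woman (2.3.1); 180 women in two groups (2.8), taken here as 90 per group since the ratio is not stated; two-sided tests at .05 and chi-square for counts (2.9). **Assumed, because the article gives no value:** the share *p* of women with a positive β-HCG, shown from 40% to 70%.

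**Step 1: the numerator.** Take one group of 90 women with 60% positive (illustrative): 54 positive women and 180 embryos transferred.

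- Both embryos credited: 2 × 54 = 108 implanted, rate 108/180 = 60%.
- One embryo credited: 54 implanted, rate 54/180 = 30%. Under this rule the rate can never exceed 50%.

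The same data give 60% or 30%. The denominator of the clinical and persistent pregnancy rates is likewise 108 or 54, so those rates also change by a factor of two.

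**Step 2: variance under each conversion, *n* women per group.** A chi-square test on embryos with success rate *r* uses the variance r(1−r)/(2n).

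- Both credited: r = p. True variance p(1−p)/n; assumed variance p(1−p)/(2n). Ratio = 2, whatever *p* is.
- One credited: r = p/2. True variance p(1−p)/(4n); assumed variance (p/2)(1−p/2)/(2n) = p(1−p/2)/(4n). Ratio = (1−p)/(1−p/2).

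**Step 3: type I error at nominal 5%** = 2 × [1 − Φ(1.96/√ratio)].

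| Conversion | p | Ratio | 1.96/√ratio | Type I error |
|---|---|---|---|---|
| Both credited | any | 2 | 1.386 | 0.166 |
| One credited | 0.40 | 0.60/0.80 = 0.750 | 2.263 | 0.024 |
| One credited | 0.60 | 0.40/0.70 = 0.571 | 2.593 | 0.010 |
| One credited | 0.70 | 0.30/0.65 = 0.462 | 2.885 | 0.004 |

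Simulation under no treatment effect agrees: 0.15 to 0.18 with both credited, and 0.024, 0.010 and 0.004 with one credited at p = 0.40, 0.60 and 0.70.

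**Step 4: the same data with the woman as the unit.** One binary result per woman, compared by chi-square, gives a simulated type I error of 0.044 to 0.053, which is nominal apart from discreteness.

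**Step 5: does the change of unit cost sample size?** The stated figure is 180. The rates in 2.8 are 86.2% and 54.2%, mean 70.2%, difference 0.32:

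n = [1.96 × √(2 × 0.702 × 0.298) + 0.842 × √(0.862 × 0.138 + 0.542 × 0.458)]² / 0.32² = 3.16/0.1024 = 30.9, so 31 per group.

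With 10% dropout, 31/0.9 = 34.4, so 35 per group and 70 in total (84 with continuity correction). The inputs therefore do not reproduce 180. That is a separate matter, and this point does not rest on it. For that planned difference, power is 99.8% with 90 women per group and 99.6% with 81. Those rates are an overall response rate, not a β-HCG-positive rate, so this shows only that a per-woman analysis needs no more women at the article's own planning figures.

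**The case against.** The strongest objection is that the embryo-level chi-square is inferred. The sentence in 2.9 is general, no section gives an embryo-level sample size, and a condensed article may leave the handling of paired embryos to an analysis plan that is not shown. There is also a natural reading of 2.6.1 in which a positive test is one success per woman. With women as the denominator, chi-square is valid, as step 4 shows.

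This stands as a limit on what can be claimed. A reader might infer that the planned test is invalid, or that false positives are inflated. The article supports neither as a flat statement: it does not commit to testing 360 embryos as independent, and the error is too high under one conversion and too low under the other. A third calculation might also tempt: embryos counted individually with clustering ignored give 7.4% to 11.0% for an assumed within-woman correlation of 0.2 to 0.5. That does not describe this plan, which does not count embryos to decide implantation.

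The mismatch itself is not met by the objection. The per-woman reading contradicts the written denominator. An analysis plan could choose a clustered model, but it could not make a blood result per woman count embryos without changing the definition.

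**Conclusion.** The numerator of the first primary outcome cannot be obtained from the measurement named for it. This follows from 2.6.1 and 2.3.1 alone and needs no assumption. It carries over to the denominators of the other two primary outcomes.

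The error-rate statement is conditional on embryos remaining the denominator and on the general chi-square sentence being applied to them. The type I error is then about 16.6% if both embryos are credited, which needs no assumed rate, and about 2.4% down to 0.4% if one is credited, for assumed positive rates of 40% up to 70%. The range shows how much depends on a rule that the article does not state; it does not measure a known bias. The definition should be corrected before the data are analysed.

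**What to change.** - **First primary outcome:** define it as women with a positive β-HCG divided by women randomised, compared by chi-square. This resolves both the measurement and the unit, and keeps the number of primary outcomes at three.
- **Embryo-level rate, only if still wanted:** make it explicitly secondary, as gestational sacs at the already planned week-5 ultrasound divided by embryos transferred, analysed by GEE or with cluster-robust standard errors by woman. It should not replace the β-HCG outcome. It leaves out implantations lost before week 5, and it comes from the same scan that defines clinical pregnancy.
- **Clinical and persistent pregnancy rates:** replace implanted embryos by women randomised as the denominator, with women as the numerator, so that no primary outcome depends on the unmeasured count.

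The cost is rewording 2.6.1. If the secondary rate is kept, add recording of the sac count at a scan already scheduled and one standard model, with a possibly wider interval. No visit is added, and the article's own planning rates call for no larger sample.

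### Clinical and persistent pregnancy rates are divided by implanted embryos, so two of the three primary outcomes do not compare the randomised groups and can hide or, under some assumptions, reverse a benefit

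*Protocol article*

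**What the plan says.** Section 2.6.1 of the protocol article names three primary outcomes and gives a formula for each.

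- Implantation: "number of embryos implanted/total number of embryos transferred". It is read from β-HCG on days 8 and 10 after transfer: "Positive results can be determined as successful embryo implantation".
- Clinical pregnancy: "Clinical pregnancy rate: number of clinical pregnancies/number of implanted embryos". The event is a gestational sac with fetal heartbeat on ultrasound at week 5.
- Persistent pregnancy: "Persistent pregnancy rate: number of cycles of continuous pregnancy/number of embryos implanted". The event is a fetal heartbeat on ultrasound at week 12.

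Under section 2.3.1, "the transferred embryos are 2 superior embryos", so each woman contributes two embryos at transfer. Under section 2.5, the formula is added to conventional treatment after transfer and taken for five weeks. Section 2.9 compares rates by chi-square test. Nowhere does the article define either pregnancy rate per woman randomised or per transfer.

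**The concern.** There are three faults in the two pregnancy definitions.

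1. **Denominator.** Whether an embryo implants is a result of the trial, and in fact its first primary outcome. A woman with no implantation adds nothing to the numerator or the denominator of the other two rates. The groups compared are then selected by an outcome that treatment may affect, and the protection of randomisation is lost.
2. **Units.** A woman can have at most one pregnancy or cycle, but up to two implanted embryos. If both implant and she is pregnant, she counts 1/2. A woman with one implanted embryo and one pregnancy counts 1/1.
3. **Counting.** A positive β-HCG is one result per woman and does not separate one implanted embryo from two. The article gives no other rule, so the denominator cannot be counted as defined.

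The article's aim is to test the formula's effect on pregnancy outcome, and these are the only two primary outcomes that follow pregnancy beyond implantation. A real gain per woman could be reported as little or no gain, or as a loss.

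**Working it through.** The article gives no implantation, survival or pregnancy rate, so there is no figure of its own to reproduce on this point. The response rates in section 2.8 are not linked to any of the three primary outcomes. The definitional faults need no arithmetic. Their effect has to be shown with assumed inputs.

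**Counting example** (assumed counts; 90 women per arm, taking the 180 as split 1:1)

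| | Control | Treatment |
|---|---|---|
| Women with one / two embryos implanted | 30 / 10 | 30 / 20 |
| Implanted embryos | 30 + 2×10 = 50 | 30 + 2×20 = 70 |
| Clinical pregnancies | 36 | 45 |
| Per woman randomised | 36/90 = 40.0% | 45/90 = 50.0% |
| As written | 36/50 = 72.0% | 45/70 = 64.3% |

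In both arms 90% of women with an implantation reach clinical pregnancy (36/40 and 45/50). The arm with more pregnancies has the lower rate as written.

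**Formulas**

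For two embryos per woman (section 2.3.1), let p be the implantation probability per embryo, ρ the within-woman correlation and s the survival of an implanted embryo to week 12, independent between embryos. Per woman:

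- both implant: q = p² + ρp(1−p)
- expected implanted embryos: 2p
- at least one implants: W = 2p − q
- persistent pregnancy: P = 2ps − qs²

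The three candidate rates are:

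- per woman randomised: P
- as written, counting 0, 1 or 2 embryos: P/(2p)
- as written, counting one implantation per β-HCG-positive woman: P/W

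**Base scenario** (assumed): p = 0.35 vs 0.50, ρ = 0.2, s = 0.85 × 0.90 = 0.765 in both arms, s² = 0.5852.

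- Control: q = 0.1225 + 0.2×0.2275 = 0.168; W = 0.532; P = 0.7×0.765 − 0.168×0.5852 = 0.437. P/(2p) = 62.5%; P/W = 82.2%.
- Treatment: q = 0.25 + 0.2×0.25 = 0.300; W = 0.700; P = 1.0×0.765 − 0.300×0.5852 = 0.589. P/(2p) = 58.9%; P/W = 84.2%.

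**Range over mechanisms** (ρ = 0.2, same formulas)

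| Arm | p | s | Per woman | As written, 0/1/2 embryos | As written, one per positive woman |
|---|---|---|---|---|---|
| Control | 0.35 | 0.765 | 43.7% | 62.5% | 82.2% |
| Better implantation only | 0.50 | 0.765 | 58.9% | 58.9% | 84.2% |
| Better survival only | 0.35 | 0.85 | 47.4% | 67.7% | 89.0% |
| Both, modest implantation gain | 0.40 | 0.85 | 53.0% | 66.2% | 89.5% |
| Both, large implantation gain | 0.50 | 0.85 | 63.3% | 63.3% | 90.5% |

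On the 0/1/2 count, better implantation alone lowers the rate as written. Every row with better survival keeps it above control. In the last row, however, a gain of 19.6 points per woman (63.3 − 43.7) appears as less than one point (63.3 against 62.5).

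On the one-per-positive-woman count, better implantation alone gives a gain of about 2 points where the gain per woman is 15.2 (58.9 − 43.7).

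**Sensitivity to ρ** (better implantation only, 0/1/2 count). At ρ = 0 the rate as written goes from 66.3% to 61.9%; at ρ = 0.4 it goes from 58.7% to 56.0%. The fall does not depend on the choice of 0.2.

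**Tests.** Simulation of the base scenario with 90 women per arm gave about 51% power per woman randomised. As written, the 0/1/2 count rejected in about 2% of trials, nearly all favouring control. Counting positive women rejected in about 6%. These figures describe that one scenario only.

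**The case against.** **The reversal needs a count that the protocol does not produce.** This stands. β-HCG yields one result per woman. If that is all that enters the denominator, the base scenario gives 82.2% to 84.2%: heavily diluted, but in the right direction. A fall on this count needs a further assumption, such as the added implantations being lost more often: 36/40 = 90% against 41/50 = 82%, while per woman randomised 36/90 = 40.0% becomes 41/90 = 45.6%.

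**The sign depends on how the formula works.** This also stands. The Introduction describes the formula's long use in threatened abortion, so an effect on survival is plausible, and then the rate as written can rise.

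**Implanted may be a translation slip for transferred.** The denominator would then be fixed at two embryos per woman, nobody would be lost and the direction would be kept: 43.7/2 = 21.9% against 58.9/2 = 29.5% in the base scenario. But section 2.6.1 uses the two words for different things within a single formula, which argues against a slip. Even then, a rate with one pregnancy over two embryos could not exceed 50%.

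**The trial still collects what is needed.** This is correct. A reader might infer that the trial cannot answer its question. The documents do not support that, because ultrasound at weeks 5 and 12 is planned and the implantation rate has a fixed denominator of transferred embryos (although its numerator shares the counting problem). The fault lies in how two rates are defined, not in the data.

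**Conclusion.** The two definitions are wrong as written. They mix units, condition on a post-randomisation result that is itself a primary outcome, leave out women whose transfer failed, and rest on a count that β-HCG cannot supply. None of this depends on an assumed rate.

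The size and direction of the distortion do. With assumed implantation of 35% vs 50%, correlation 0.2 and unchanged survival of 0.765, a rise from 43.7% to 58.9% per woman becomes a fall from 62.5% to 58.9% on the 0/1/2 count, or a rise from 82.2% to 84.2% when positive women are counted. With survival also improved to 0.85, the rate as written stays above control.

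A reader might infer that a working treatment will look harmful. The documents do not support that: they give no implantation or survival rates and do not settle the count. The supported conclusion is that neither rate compares the randomised groups, and that either can hide or reverse a benefit.

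**What to change.** Redefine both outcomes in section 2.6.1 per woman:

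- Clinical pregnancy rate = women with a gestational sac and fetal heartbeat at week 5 / all women randomised to the arm.
- Persistent pregnancy rate = women with a fetal heartbeat at week 12 / all women randomised to the arm.

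Report any ratio per implantation as descriptive only.

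The change is to wording alone. Visits, measurements and the planned chi-square test stay the same, each woman counts once, and the redefinition by itself requires no extra patients. For orientation, 81 evaluable women per arm (90 less 10%, assuming 1:1 allocation) give 80% power for a difference of about 21 to 22 percentage points in a per-woman rate, at assumed control rates of 30% to 54%.
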